#### Validation of observational results against ARISTOTLE data

In Objective 1 alone, we will validate the findings from our primary analysis against ARISTOTLE by determining whether results are compatible with the trial results. ARISTOTLE demonstrated superiority of apixaban over warfarin for the primary endpoint (HR 0.79, 95% CI 0.66 to 0.95).^7^ The treatment effect seen with EHR data may be weaker than that seen in ARISTOTLE.

An analysis of EU patients in ARISTOTLE showed a smaller treatment difference for the primary endpoint and death: HR for stroke/SE 0.92 (95% CI 0.56 to 1.52), all-cause death 0.89 (95% CI 0.68 to 1.18). The European Medicines Agency Assessment Report suggested the smaller treatment effect may have been due to superior INR control in the warfarin arm of the EU subgroup (median time in therapeutic range (TTR) 68.93%)^15^; this study could provide additional evidence on this point.

Either a result of superiority or non-inferiority will be considered compatible with ARISTOTLE results. We have set two criteria that must be met to conclude results are consistent with the trial result:

The effect size must be clinically comparable with the ARISTOTLE findings; the HR for time to stroke/SE with the EHR must be between 0.69 and 0.99. This range is not symmetrical around the ARISTOTLE estimate of 0.79 as it is anticipated the treatment effect in routine clinical care may be weaker than that seen in the optimised setting of a clinical trial.The upper limit of the 95% CI for the rate ratio must be less than 1.52 (upper limit in the EU subgroup of ARISTOTLE).

In addition, if the upper limit of the 95% CI is less than 1 then superiority of apixaban versus warfarin will be concluded.

In order to understand the extent to which the EHR population resembles the ARISTOTLE trial population the absolute event rates of the outcomes will be compared.

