## Methods and analysis

Figure 1 (figure adapted from a study in real-world effects of medications for chronic obstructive pulmonary disease^10^) provides an overview of the study, covering the objectives and data sources used, and how RCT data will be used in Objective 1 to validate methods for analysing effectiveness of treatments for stroke prevention in AF in non-interventional data. Should Objective 1 prove successful the validated methods will be applied to unanswered questions in Objectives 2 and 3.

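### At the planned size the 1.52 limit adds nothing to the ARISTOTLE validation rule, so validation rests on the point estimate alone and a true HR of 1.00 would pass about 46% of the time

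*Protocol article*

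**What the plan says.** The rule is in the protocol article, Statistical analysis, under Validation of observational results against ARISTOTLE data. It opens with "We have set two criteria that must be met to conclude results are consistent with the trial result".

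- Criterion 1: "the HR for time to stroke/SE with the EHR must be between 0.69 and 0.99". The article explains that the window is deliberately asymmetric around 0.79, because the effect in routine care may be weaker.
- Criterion 2: the "upper limit of the 95% CI for the rate ratio must be less than 1.52 (upper limit in the EU subgroup of ARISTOTLE").

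Two further sentences bear on the rule. Before the criteria: "Either a result of superiority or non-inferiority will be considered compatible with ARISTOTLE results". After them, as an addition: "if the upper limit of the 95% CI is less than 1 then superiority of apixaban versus warfarin will be concluded".

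The benchmark is the trial result, "primary endpoint (HR 0.79, 95% CI 0.66 to 0.95"). The value 1.52 comes from the EU subgroup, "HR for stroke/SE 0.92 (95% CI 0.56 to 1.52").

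The opening of Methods and analysis gives the consequence of passing: "Should Objective 1 prove successful the validated methods will be applied to unanswered questions in Objectives 2 and 3". The Figure 1 legend treats comparable results as showing that the CPRD sources are reliable for studying these treatment effects.

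**The concern.** A two-part rule suggests two safeguards: one on the size of the estimate and one on its precision. The second limit, however, is the edge of a wide interval from a small subgroup. It reflects how little information that subgroup carried, not how much loss of effect would be tolerable. Set against a cohort of about 18 000, it may never come into play. In that case nothing in the pass/fail rule takes account of uncertainty, and a window ending at 0.99 captures nearly half of any sampling distribution centred on 1.

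Objectives 2 and 3 depend on this result. They cover patient groups and drug comparisons for which ARISTOTLE gives no benchmark, so an error let through at validation would be hard to detect later.

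**Working it through.** **Inputs from the protocol article**

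- Window 0.69 to 0.99, upper limit 1.52, ARISTOTLE 0.79 (0.66 to 0.95), EU subgroup 0.92 (0.56 to 1.52): validation section.
- Two-sided 95% CIs and censoring at 5 years: Methods of analysis.
- About 18 000 patients matched 1:1: Objective 1, Step 3. ARISTOTLE had 18 201.
- Number of EHR stroke/SE events: not given. Assumed equal to ARISTOTLE's information, and varied from 100 to 1500.

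**Checks on the plan's own figures.** 23 526 × 0.60 = 14 115.6, and adding 8400 gives 22 515.6, which agrees with the stated 14 115 and >22 000. Both quoted intervals are symmetric on the log scale: √(0.66 × 0.95) = 0.792 and √(0.56 × 1.52) = 0.923. The SE can therefore be recovered from them.

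**Information in each interval.** SE = ln(upper/lower)/(2 × 1.96); with 1:1 allocation, events ≈ 4/SE².

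- ARISTOTLE: ln(0.95/0.66)/3.92 = 0.0929, about 463 events.
- EU subgroup: ln(1.52/0.56)/3.92 = 0.255, about 62 events.

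**When criterion 2 can matter.** At the highest passing estimate, 0.99, the upper limit reaches 1.52 only if SE ≥ ln(1.52/0.99)/1.96 = 0.219. That is about 83 or fewer events, or 83/18 000 = 0.46% of patients over up to 5 years. ARISTOTLE's interval implies 463/18 201 = 2.5%. At an estimate of 0.79 it would take about 35 or fewer events. At SE 0.0929, an HR of 0.99 has upper limit 0.99 × exp(1.96 × 0.0929) = 1.19.

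**Chance of passing.** With criterion 2 inactive, P(pass | h) = Φ[ln(0.99/h)/SE] − Φ[ln(0.69/h)/SE]. At h = 1.00 this is Φ(−0.108) − Φ(−3.99) = 0.457.

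**Split by whether the interval excludes 1.** An upper limit below 1 needs HR < exp(−1.96 × 0.0929) = 0.834. So P(in window and upper limit < 1 | h) = Φ[ln(0.834/h)/SE] − Φ[ln(0.69/h)/SE].

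| True EHR HR | Pass | of which upper limit < 1 | of which upper limit ≥ 1 |
|---|---|---|---|
| 0.79 | 92.0% | about 65% | about 27% |
| 0.92 | 78.4% | about 14% | about 64% |
| 1.00 | 45.7% | about 2.5% | about 43% |

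The pass rate is 26% at a true HR of 1.05 and 13% at 1.10.

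**Sensitivity to the unknown event count, true HR 1.00.** 44.8% at 100 events, 46.7% at 200, 46.0% at 400, 45.1% at 600, 43.7% at 1000 and 42.3% at 1500. Removing criterion 2 changes none of these.

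**Superiority sentence.** At SE 0.0929 an HR of 0.65 has an interval of 0.54 to 0.78. The upper limit is below 1, but criterion 1 fails.

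**The case against.** Much of the leniency is declared and reasoned. The article expects a weaker effect in routine care, points to the EU subgroup with its better INR control, and accepts non-inferiority. That subgroup's interval includes 1, so a near-null EHR result is not by itself proof of a failed method. This stands, and the asymmetric window should be kept. A reader might object that 0.67, inside ARISTOTLE's interval, fails while 0.97, outside it, passes. That only restates an asymmetry which the article announces and explains; it is not an error.

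Two stronger readings are tempting and are not supported.

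- That 1.52 can never bind. It could with about 83 or fewer events, for example if matching shrank the cohort drastically, and the article does say that sample size will be traded against balance. The redundancy holds at the planned size.
- That the rule cannot tell a working method from one returning no effect. It does separate them, 92% against 46%, but weakly.

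The superiority sentence can be read as applying only after both criteria are met, and that may be what is intended. Read literally it carries no such condition. This is an ambiguity to close, not proof that superiority would be claimed after failed validation.

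The absolute event rates, the on-treatment, adherence and INR analyses and the discussion of residual confounding all help interpretation, but none is a pass/fail condition. An article may leave operating characteristics to the full protocol, so their absence is not criticised. The rule itself is stated in full and described under Limitations as prespecified, so it can be judged as it stands.

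**Conclusion.** The point holds for the planned study and should be fixed. Once the estimate is in the window, the 1.52 limit has no effect unless there are about 83 or fewer stroke/SE events. Validation then depends on the point estimate alone. A pass is about twice as likely at a true HR of 0.79 as at 1.00 (92.0/45.7 = 2.0), which is weak support for calling the data reliable.

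The figures rest on a normal approximation for log HR, 1:1 matching and ARISTOTLE-like precision. The 46% hardly depends on the last of these (42% to 47% from 100 to 1500 events). The 92% and 78% depend on it more: at 300 events they are 85% and 73%.

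The split by interval shows where the evidence lies. A pass with an upper limit below 1 is far more likely at 0.79 than at 1.00 (about 65% against 2.5%). A pass with an upper limit of 1 or above is more likely at 1.00 (about 43% against 27%).

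**What to change.** Changes to wording only, made before the outcome analysis:

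1. Keep the 0.69 to 0.99 window. Remove 1.52 as a working non-inferiority check, or replace it with a margin that is clinically justified in advance and can bind at the expected event count.
2. Report two levels of success. (a) HR in the window and upper 95% limit below 1: *trial benefit reproduced*. (b) HR in the window and upper limit 1 or above: *compatible with ARISTOTLE but not distinguishable from no effect*.
3. Let Objectives 2 and 3 carry the level reached. Do not describe level (b) as showing that the data are reliable for treatment effects.
4. State that superiority is concluded only when the validation criteria are also met, and qualify the sentence accepting either superiority or non-inferiority in the same way.

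There is no data cost. The price is a demanding top level: at this precision it is reached in about 65% of cases at a true HR of 0.79, 14% at 0.92 and 2.5% at 1.00. The other in-window results fall in level (b). Because Objectives 2 and 3 may still proceed from level (b), this does not lower the chance that a null method goes forward; it makes the strength of the validation visible when it does.

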#### Sensitivity analyses

Primary and secondary effectiveness outcomes will also be analysed using the on-treatment censoring scheme to investigate whether the extent of treatment discontinuation compromises confidence in the effectiveness analyses.

Exclusion of patient time post-treatment discontinuation in the safety and sensitivity analyses might bias results towards a conclusion of no difference^16^ and risks selection bias due to attrition^17^; the set of patients who switch or discontinue treatment will therefore be examined to ascertain whether biases of this nature may have occurred.

Additional analyses may be performed using methods such as inverse probability of censoring weighting (IPW) or a rank-preserving structural failure time model to estimate the treatment effect that would have been observed in the absence of treatment switching. We will explore the impact of time-varying eligibility by using methods such as a modified treatment strategy IPW.^17^

Adherence will be estimated in the EHR cohort to enable comparisons with the trial and investigate the extent to which this may have influenced differences in treatment effect observed. For apixaban, we will calculate the proportion of days covered (PDC) over a patient’s time when on treatment as a measure of adherence. Warfarin dose is poorly recorded in EHR, therefore warfarin adherence will be estimated by looking at adherence to other long-term daily medications as a proxy measure and by looking at INR control by calculating per cent INR TTR as a measure of overall warfarin treatment regime adherence.

We will perform a supplementary analysis in patients deemed adherent (PDC ≥80% matching ARISTOTLE compliance limit) along with an exploratory subgroup analysis by INR TTR. The different nature of the proxy variables used for adherence in the DOACs (PDC) compared with warfarin (INR TTR) means that the adherence estimates may not be comparable; should great differences in adherence be observed between these exposure groups the definitions of adherence used may need to be reassessed.

Apixaban was a newly available drug with a low number of patients having a prescription in the first year it was available^18^; we will therefore perform a sensitivity analysis with the start of the study period shifted forwards a year to January 2014 to investigate the impact of inclusion of early adopters who may differ from later adopters of a new drug.

#### Plan for addressing confounding

In the study period, apixaban was a newly available treatment leading to the possibility of channelling bias. For Objective 1, by applying trial eligibility criteria to both treatment cohorts and matching using the baseline covariates we should avoid channelling bias. To handle confounding, treatment arms will be matched using the optimal method selected. Unmeasured or unknown confounding may remain and this will be explored in the analysis and discussion of results.

#### Missing baseline data

UK EHR data have been shown to be almost complete for drug prescribing and information on important comorbidity is well recorded. For some variables such as renal function and alcohol intake, a patient is more likely to have no data entered if there is no overt clinical evidence of abnormality; in such cases, we may take a pragmatic approach categorising into a parameter (‘evidence of’ vs ‘no evidence of’) with those with no data included in the ‘no evidence of’ group. For BMI and SBP, we cannot assume data are missing at random as we expect a patient is less likely to have these recorded if they appear at a healthy weight and do not have hypertension, respectively, or if they have a lower comorbidity burden. Furthermore, as the proportion of patients with missing baseline BMI or SBP is expected to be low (approximately 4% for BMI and <1% for SBP^18^), these patients will be excluded from the trial-eligible cohort.

#### Missing prescription data

Treatment may be initiated in secondary care, meaning the first prescription of patients newly initiating treatment or switching treatments is missing; to account for this we will perform a sensitivity analysis where those newly initiating treatment are assigned an earlier derived index date. Hospitalised patients may have prescriptions in secondary care leading to treatment gaps in their primary care data. We will investigate the occurrence of hospitalisation around treatment discontinuation and assess the potential impact on the results of missed events by performing a sensitivity analysis with different extended derived dates of last dose. Some concomitant drugs used in determining eligibility and matching patients are available over the counter (OTC), meaning we may miss that patients are exposed to these; we expect OTC use of these drugs to be similar in both treatment groups.

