### Setting/data sources

Patient data used in this study will be obtained from several sources: primary care data on UK National Health Service (NHS) patients from Clinical Practice Research Datalink (CPRD) Gold and Aurum databases, additional data on hospital events and mortality on UK NHS patients with linked data from the Hospital Episodes Statistics (HES) and Office for National Statistics (ONS) databases, and results from the ARISTOTLE trial.

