**Figure 2 F2:**
[figure not shown]
Flow chart illustrating the assembly of a matched trial-analogous cohort of EHR patients. AF, atrial fibrillation; CPRD, Clinical Practice Research Datalink; EHR, electronic health record.

##### Step 1

We will select all (HES and ONS linked) patients in the EHR cohort (CPRD Gold and Aurum) who would have met the following *inclusion* criteria for the ARISTOTLE study, at least 6 months after patient registration in the database on or prior to the index date:

Diagnosis of AF.Age 18+ years.One or more stroke risk factors (age 75 years or older; prior stroke, transient ischaemic attack or SE; congestive heart failure; diabetes mellitus; hypertension).

In ARISTOTLE, patients randomised to apixaban were new users of apixaban while both treatment arms were allowed to be previous users of warfarin, with patients stratified by prior warfarin/VKA exposure. To mirror ARISTOTLE, we will assess trial criteria for apixaban patients on the date of their first prescription of apixaban while allowing patients prescribed warfarin to become eligible at any warfarin prescription date during the study period; furthermore, we will match ARISTOTLE in the proportion of new versus prevalent users in both treatment arms. We will then exclude patients who meet any of the following ARISTOTLE study *exclusion* criteria prior to their eligible-for-inclusion date:

AF due to reversible causes.Mitral stenosis.Increased bleeding risk.Conditions other than AF requiring chronic anticoagulation.Persistent, uncontrolled hypertension.Active infective endocarditis.Current treatment with aspirin >165 mg/day.Simultaneous current treatment with both aspirin and a thienopyridine.Conditions likely to interfere with participation in the trial or cause death within 1 year.Recent alcohol or drug abuse, or psychosocial reasons making study participation impractical.Recent ischaemic stroke (within 7 days).Severe renal insufficiency.Alanine aminotransferase or aspartate aminotransferase >2× upper limit of normal (ULN) or total bilirubin ≥1.5× ULN.Platelet count ≤100 x10^9^/LHaemoglobin <90 g/L.Pregnancy or breast feeding.

Feasibility counts in Gold found approximately 60% of patients with AF prescribed apixaban met the ARISTOTLE trial criteria. Details of the algorithms used in applying the trial criteria to the EHR data are given in the online supplemental file.

10.1136/bmjopen-2020-042947.supp1Supplementary data

##### Step 2

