We will select a subset of apixaban patients from our EHR pool to create a cohort that matches the ARISTOTLE apixaban participants on a selection of the following baseline characteristics:

Age.Sex.Body mass index (BMI).Systolic blood pressure (SBP).Congestive heart failure or left ventricular systolic dysfunction.Hypertension requiring treatment.Diabetes mellitus.Prior stroke/thromboembolism.Smoking status.Alcohol consumption.Level of renal impairment.Prior VKA/warfarin exposure.Labile INR in prior users of warfarin.Concomitant use of: aspirin, antiplatelet or non-steroidal anti-inflammatory drug, lipid-lowering drug therapy, or CYP3A4 inhibitor.

This step will generate a group of ARISTOTLE-analogous apixaban patients, with similar baseline characteristics to ARISTOTLE subjects at the point of randomisation (n~9000).

The variables selected are expected to influence the likelihood of the outcomes of interest. Exact selection of matching variables will depend on the quality and completeness of the data available and a balance will be struck between matched sample size and balance. Different methods to facilitate selection of a matched cohort will be explored, such as propensity score matching (PSM) and coarsened exact matching (CEM),^13^ a non-parametric method that may give estimates with lower variance and bias for a given sample size compared than other methods.^14^

##### Step 3

The resulting trial matched sample of EHR apixaban patients will be matched to the warfarin ARISTOTLE-eligible EHR patients (figure 2) using a matching method such as PSM or CEM (final method selected based on giving optimal sample size vs balance). Risk set sampling will be employed in order to ensure similar duration of prior VKA/warfarin exposure for the prevalent users in the apixaban and warfarin EHR cohorts. The covariates for consideration in matching between EHR treatment arms or construction of a propensity score (PS) model will include the variables listed in step 2 along with additional EHR variables such as data source (Gold or Aurum), socioeconomic status and comorbidities. Each apixaban patient from the ARISTOTLE-eligible EHR patients will be matched 1:1 with the warfarin EHR patient with the closest match giving a trial-analogous cohort of ~18 000.

##### Step 4

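### Secondary-care initiation is handled only by moving the index date, which cannot balance the arms on setting of initiation; no named matching variable captures a recent admission

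*Protocol article*

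**What the plan says.** In the section on missing prescription data, the article notes that "Treatment may be initiated in secondary care, meaning the first prescription of patients newly initiating treatment or switching treatments is missing". The response is that "we will perform a sensitivity analysis where those newly initiating treatment are assigned an earlier derived index date". The same section uses hospitalisation again, but only at the other end of exposure: "We will investigate the occurrence of hospitalisation around treatment discontinuation".

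Matching between arms (Objective 1, Step 3) uses the Step 2 list plus "additional EHR variables such as data source (Gold or Aurum), socioeconomic status and comorbidities". The Step 2 list covers demographics, lifestyle, blood pressure, chronic conditions, prior stroke without recency, concomitant drugs and prior vitamin K antagonist (VKA) exposure. The final choice is left open: "Exact selection of matching variables will depend on the quality and completeness of the data available". The Cox model (Methods of analysis) contains treatment and prior VKA status only.

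Step 1 requires every Objective 1 patient to be linked to the Hospital Episode Statistics (HES) data. The section on data sources says that linkage gives "additional data on hospital events and mortality on UK NHS patients with linked data from the Hospital Episodes Statistics". The plan for addressing confounding says that trial eligibility criteria plus matching should avoid channelling bias, and that residual confounding will be explored.

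**The concern.** A missing first prescription and a hospital start are two different problems. The first puts time zero in the wrong place. The second may mean that the patient started treatment just after an acute event. Shifting the index date addresses the first and leaves the second untouched.

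A patient whose first GP prescription follows a recent discharge may carry a different risk from one started electively with the same age, comorbidities and stroke history. The only recency rule for stroke is the exclusion of ischaemic stroke within 7 days, so a start two weeks after a stroke admission can be matched to a patient whose stroke was years ago. The drugs may also differ in where they are started: the background section says that warfarin needs frequent INR monitoring and that direct-acting agents were expected to be easier to manage.

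The stakes are those of a gate. Objective 1 must give a hazard ratio between 0.69 and 0.99 before the methods are carried into Objectives 2 and 3. Randomisation balanced this factor in ARISTOTLE; here only matching can.

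**Working it through.** The plan gives no figure on this point, so there is none of its own to reproduce. Its only worked numbers are the feasibility counts, which do reproduce (0.60 × 23 526 = 14 115.6; adding 8400 gives 22 515.6) and do not bear on the question.

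**Inputs from the document.** Validation range 0.69 to 0.99; ARISTOTLE hazard ratio 0.79; EU subgroup hazard ratio 0.92 (all in the section on validation against ARISTOTLE).

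**Assumed inputs, not in the document.**
- RR, the stroke/systemic embolism rate ratio for hospital starters given the matched covariates: 1.5 or 2, constant over follow-up.
- Share of hospital starts among VKA-naive patients: 20% in one arm, 30% or 40% in the other.
- w, the share of statistical information from VKA-naive patients: 0.5, with the VKA-experienced stratum taken as unbiased.
- A true hazard ratio of 1.05, to test for false validation.

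**Formulas.** Bias factor in naive patients: B = [1 + p₁(RR − 1)] / [1 + p₀(RR − 1)], where p₁ is the larger share and p₀ the smaller. Pooled factor: B^w. The observed hazard ratio is the true one multiplied by B^w if hospital starts are commoner on apixaban, and divided by it if commoner on warfarin.

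| RR | Shares | B (naive) | B^0.5 (pooled) | 0.79 × / ÷ | 0.92 × | 1.05 ÷ |
|---|---|---|---|---|---|---|
| 1.5 | 30% v 20% | 1.15/1.10 = 1.045 | 1.022 | 0.808 / 0.773 | 0.941 | 1.027 |
| 1.5 | 40% v 20% | 1.20/1.10 = 1.091 | 1.044 | 0.825 / 0.756 | 0.961 | 1.005 |
| 2 | 30% v 20% | 1.30/1.20 = 1.083 | 1.041 | 0.822 / 0.759 | 0.958 | 1.009 |
| 2 | 40% v 20% | 1.40/1.20 = 1.167 | 1.080 | 0.853 / 0.731 | 0.994 | 0.972 |

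**Pooled factor needed to cross a limit.** From 0.79: 0.99/0.79 = 1.253 upward or 0.69/0.79 = 0.873 downward. From 0.92: 0.99/0.92 = 1.076. From 1.05: 0.99/1.05 = 0.943. At w = 0.5 only the last row crosses a limit, and it does so narrowly (0.994 against 0.99).

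**Sensitivity to the assumptions.** With RR 2 and 40% v 20%, a true 0.92 becomes 0.964 at w = 0.3 and 1.025 at w = 0.7; a true 1.05 in the reverse direction becomes 1.003 and 0.943. With RR 1.25 and w = 0.5, the pooled factor is only 1.012 to 1.024 and no verdict changes.

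These figures test the hazard-ratio range alone, not the second criterion (upper confidence limit below 1.52).

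**The case against.** The Step 3 list is introduced as examples, the final selection is deferred, and this is a condensed article, so a recent-admission variable may yet be used. Confounding also needs two premises that the document does not state: that hospital initiation predicts stroke after matching, and that its frequency differs by drug. Step 1 already removes ischaemic stroke within 7 days and conditions likely to cause death within a year, and matching takes in prior stroke, heart failure, renal function and comorbidities, so the residual rate ratio could be well below 2. A short-lived excess after discharge would be further diluted over up to 5 years of follow-up. All of this stands, and it limits how firmly a size can be claimed.

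It does not remove the point. The article is not merely silent: it names the phenomenon and states a remedy that cannot balance setting. The expectation that matching avoids channelling bias covers only what is matched on, or what the matched variables track closely.

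Two stronger readings are tempting. A reader might infer that hospital starts can push a true 0.79 below 0.69, because 0.79/1.167 = 0.68. That is a VKA-naive hazard ratio. The criterion applies to the Objective 1 cohort as a whole, which mixes new and prevalent users in ARISTOTLE's proportions. To bring the pooled value from 0.79 to 0.69 with B = 1.167, naive patients would have to carry ln(0.79/0.69)/ln(1.167) = 0.88 of the information; nothing in the document suggests so large a share. A reader might also infer that hospital initiation can be read directly from HES. The document says only that the linkage supplies hospital events, so an admission before the first GP prescription is a proxy for where the drug was started.

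**Conclusion.** The point holds as a worthwhile, inexpensive improvement. The stated remedy moves time zero and leaves any imbalance in setting of initiation where it was; no named covariate or model term addresses it.

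The size is conditional on assumed inputs. With RR 1.5 to 2 and shares differing by 10 to 20 points, the bias factor is about 1.04 to 1.17 in VKA-naive patients and about 1.02 to 1.08 on the pooled hazard ratio if they carry half the information. A true effect at the ARISTOTLE value stays within the validation range throughout. The gate is exposed when the true effect lies near the EU subgroup's 0.92 or just above 1: at the upper end of the assumptions, 0.92 reaches about 0.99 and could fail, and 1.05 reaches about 0.97 and would meet the range criterion. The plan itself expects a weaker effect in routine care, so the first of these is relevant. Confidence in the size is low, because neither the risk difference nor the difference by drug is given.

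**What to change.** In Objective 1, Step 3, derive from HES a flag for hospital discharge within a fixed window (for example 30 days) before the first GP prescription, and describe it as a proxy for hospital initiation. Include it in the propensity score or matching set for VKA-naive starters and show its balance by arm before and after matching. The table before matching also tests the premise: if the shares do not differ by drug, the concern falls away. Add a sensitivity analysis restricted to starts without a recent discharge. Keep the planned index-date analysis, which answers a different question.

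The cost is one derived variable from data already linked for every Objective 1 patient, some misclassification (starts outside an admission are missed, and unrelated discharges are counted), and probably a small loss of matched pairs.
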